### Analyses

The statistical data analysis will be carried out using statistical analysis software. The analytic code will be documented and stored to ensure that the statistical analyses can be reproduced at a later date. For descriptive data analysis, the appropriate summary measures will be calculated according to data type, including measures of central tendency and spread for continuous data (arithmetic mean, SD, median, IQR, minimum, maximum, and range) and frequency, proportions, or percentages for categorical data. 95% CIs will be calculated for recruitment and drop-out rates, for adherence data, and for data completeness. Because this is a pilot study, no confirmatory inferential statistical analysis or hypothesis testing will be conducted.

An exploratory group comparison (descriptive analysis and 95% CIs) will be described for the secondary (clinical) outcome measures for both intention-to-treat and per-protocol approaches. In intention-to-treat analysis, the pattern of missing data will be assessed, but due to the small sample size no imputation of missing data will be conducted. However, we will conduct sensitivity analyses based on the minima and maxima from complete cases for each missing variable, to evaluate the potential impact of missing data in the sense of a best and worst case scenario.

The qualitative data analysis will be conducted according to the framework analysis method [48] and using qualitative data analysis software. Recordings of the patient interviews and the focus groups with health care professionals will be transcribed verbatim by a professional transcription agency. The transcripts will be checked for accuracy against the original recordings. In the reporting of qualitative findings, care will be taken to preserve the anonymity of patients and health care professionals. Relevant themes and categories from qualitative analysis will be triangulated with corresponding quantitative data to describe a comprehensive picture. Questionnaire scores for usability and acceptability of the aktivplan app will be interpreted in relation to the possible score range for each questionnaire.

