## Introduction

### Background

Cardiovascular disease (CVD) remains the most common cause of death worldwide, with 18.6 million deaths attributed to CVD in 2019 [1]. In Austria, CVD was the most common cause of death in 2022 (34.3% of all deaths) and the most frequent discharge diagnosis for all acute hospital admissions (11.6%) [2]. Cardiac rehabilitation constitutes an important care pathway for the secondary prevention of CVD [3,4]. Cardiac rehabilitation programs aim to support patients in implementing a lifelong heart-healthy lifestyle, including regular physical activity, for example, through joining cardiac exercise groups or through self-directed training at home [3]. As a general recommendation, patients should carry out aerobic physical activity at a moderate or moderate-to-high intensity at least 3 times per week, and ideally 6 to 7 times per week. Aerobic physical activity should amount to at least 150 minutes per week at moderate intensity, or 75 minutes per week at vigorous intensity, or an equivalent combination thereof. In addition, patients should perform muscle-strengthening exercises for the large muscle groups twice per week with 8 to 15 repetitions per set. The overall training volume should amount to an energy expenditure of 1000 to 2000 kcal per week [5-7].

High-level scientific evidence demonstrates the effects of cardiac rehabilitation programs on reducing long-term morbidity and mortality. Cardiac rehabilitation has therefore received the highest class of recommendation in clinical guidelines for patients with chronic heart failure, chronic cardiovascular risk, after myocardial infarction with ST-elevation, after myocardial revascularization, and for CVD prevention in clinical practice [6]. The cardiac rehabilitation pathway is organized according to phases, whereby phase I describes the period of acute hospital admission. Phase II describes a structured and supervised program, delivered in an inpatient or outpatient setting and lasting several weeks. It aims to provide patients with the knowledge and awareness of the health-promoting effects of regular physical activity and other heart-healthy lifestyle choices, and to impart the skills to effectively plan and implement these CVD preventive behaviors [5,6].

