### Study Design

This is a multicenter, mixed method, randomized controlled pilot study. Forty patients undergoing phase II rehabilitation will be recruited from 2 study sites (20 patients per site). Study participants will be individually randomized to the intervention group (aktivplan digital health intervention) or control (standard care, ie, not including any routinely provided digital technologies) and will be followed up for 10 weeks after discharge from phase II rehabilitation.

The reporting of this study protocol adheres to the SPIRIT (Standard Protocol Items: Recommendations for Interventional Trials) statement [21], the CONSORT (Consolidated Standards of Reporting Trials) statement extension to randomized pilot and feasibility trials [22], and the TIDieR (Template for Intervention Description and Replication) checklist [23]. The SPIRIT, CONSORT, and TIDieR checklists are provided as Multimedia Appendices 1-3.

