### Sample Size

The sample size of 40 patients (20 patients per site) reflects the typical sample size for a clinical pilot study [27] and allows the detection of problems (eg, participant withdrawals) with a prevalence of 7.5% with 95% confidence [28]. This sample size is not powered for statistical hypothesis testing of intervention effectiveness because this is not the purpose of this study.

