### Randomization

Participants will be individually randomized to the intervention or control group. Randomization will be stratified by study site, participant sex, and participant exercise capacity (peak power <1.3 Watts/kg, 1.3-1.8 Watts/kg, and >1.8 Watts/kg in incremental cycle ergometry). The randomization schedule will be prepared in advance by the study statistician who is not involved in participant recruitment. The *blockrand* package of the statistical program R (R Foundation for Statistical Computing) will be used [29]. The package enables the randomized allocation of participants for clinical and experimental studies in which participants are recruited individually and sequentially. The randomization schedule will be stored securely at the study sponsor’s office (Ludwig Boltzmann Institute for Digital Health and Prevention), which is at a different location to the study sites. Random allocation is concealed, as personnel at the study sites have no access to the randomization schedule. After a new study participant has been recruited, the site principal investigator informs the study sponsor of the patient’s sex and exercise capacity, and the randomization result is then returned to the site principal investigator.

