#### aktivplan Use Tracking

During the 10-week intervention period, use of the aktivplan app will be automatically tracked, including participants’ log-in and duration, planned physical activity sessions that have been marked as completed by participants, and additional physical activity sessions that participants enter into the app. Adherence will be quantified as a percentage of planned physical activity sessions that have been marked as completed by participants. Engagement with the app will be quantified by the time spent interacting with the app. Notably, longer duration of interaction with the app does not necessarily equate to meaningful engagement in the sense of adherence to the personal physical activity plan.

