### Outcomes

The primary outcomes address the primary study aim, that is, to pilot and assess the feasibility of a future randomized controlled trial design to investigate the effectiveness of the aktivplan digital health intervention; and to assess the usability, user experience, and acceptance of the aktivplan app. The primary outcomes are presented in Textbox 3.

The secondary outcomes address the secondary study aim, that is, the collection of clinical outcomes to inform the sample size calculation for a future definitive effectiveness trial and to provide evidence toward demonstrating patient safety of the intervention. The secondary outcomes are presented in Textbox 4.

Primary outcomes.Recruitment rate (number of recruits per week, percentage of screened patients who were recruited, and percentage of eligible patients who were recruited)Drop-out rate (number of drop-outs at the 10-week follow-up and percentage of recruited patients who dropped out)Data completeness (percentage of missing data fields in study database)Adherence to the aktivplan digital health intervention (automated use logging of the aktivplan app and video recording of the aktivplan physical activity planning session)Usability of the aktivplan app (mHealth App Usability Questionnaire)User experience of the aktivplan app (AttrakDiff mini questionnaire)User acceptance of the aktivplan app (Mobile App Rating Scale and Unified Theory of Acceptance and Use of Technology 2)Technical reliability of the aktivplan app (number and types of technical problems and qualitative data)Use of alternative and additional strategies for supporting physical activity (number and types of additional strategies and qualitative data)Experiences and perspectives of rehabilitation professionals regarding the intervention and study procedures (qualitative data from focus groups)

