## Results

Recruitment commenced on October 2, 2023. The study was completed with 34 participants recruited by May 2024, and all data were collected by August 2024. Currently, the data of the study are being analyzed and prepared for publication. The first publication of results is expected for summer 2025.

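### A 95% CI for data completeness computed over database fields would be too narrow; the participant should be the unit, and for adherence this only needs confirming

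*Protocol article*

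**What the plan says.** The primary outcomes list in the Outcomes section includes "Data completeness (percentage of missing data fields in study database". Numerator and denominator are both fields; no per-participant version is given. Drop-out rate is a separate primary outcome in the same list.

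The Analyses section then says that "95% CIs will be calculated for recruitment and drop-out rates, for adherence data, and for data completeness". It names neither the interval method nor the unit of analysis, and within-participant correlation is not mentioned. The same section rules out hypothesis testing.

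For adherence, the section on aktivplan use tracking says: "Adherence will be quantified as a percentage of planned physical activity sessions that have been marked as completed by participants". It does not say whether this is one percentage per participant or one pooled over all sessions. The same paragraph and the description of the intervention both speak of each patient's personal activity plan.

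On numbers, the plan was 40 participants, and the Results section reports: "The study was completed with 34 participants recruited by May 2024".

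**The concern.** Fields from one person are not independent. The data collection sections place a large share of the measurements at week 10: blood tests, ergometry, most questionnaires, the interview, and the return of the sensors. A participant lost before then leaves all of these blank at once. A proportion interval over all fields would take several thousand fields as the sample size, although the information comes from 34 to 40 people.

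What is at stake is how well a primary feasibility outcome appears to be known. A definitive trial would be planned partly from this study's data, and an interval of under one percentage point would suggest a precision that 34 people cannot give.

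A second, smaller matter is that a percentage over the whole database mixes skipped items with fields lost through drop-out. The two call for different remedies in a later trial.

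**Working it through.** **The article's own precision figure.** It gives no CI width for completeness or adherence. Its one precision statement is that 40 patients allow detection of a problem of 7.5% prevalence with 95% confidence. This reproduces: 1 − 0.925^40 = 0.956, and ln(0.05)/ln(0.925) = 38.4, so 39 suffice. That statement counts participants, not fields.

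**Inputs for completeness.**
- From the article: n = 34 achieved, 40 planned.
- Assumed: m = 50 to 300 fields per participant, 10% missing, ICC 0.01 to 0.30.

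**Formulas.** Design effect DE = 1 + (m − 1) × ICC. An interval over fields is too narrow by the factor √DE, which depends neither on n nor on the percentage missing.

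| ICC | m = 50 | m = 100 | m = 200 | m = 300 |
|---|---|---|---|---|
| 0.01 | 1.22 | 1.41 | 1.73 | 2.00 |
| 0.05 | 1.86 | 2.44 | 3.31 | 3.99 |
| 0.10 | 2.43 | 3.30 | 4.57 | 5.56 |
| 0.30 | 3.96 | 5.54 | 7.79 | 9.52 |

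**Example, n = 34 and m = 200 (6,800 fields).** The field-level half-width is 1.96 × √(0.1 × 0.9/6800) = 0.71 percentage points. Coverage is from a beta-binomial simulation of 20,000 runs, comparing a pooled Wilson interval with a t-interval across participants.

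| ICC | DE | Half-width allowing for clustering | Coverage, pooled | Coverage, participant-level |
|---|---|---|---|---|
| 0.01 | 2.99 | ±1.23 | 74% | 95% |
| 0.05 | 10.95 | ±2.36 | 44% | 94% |
| 0.10 | 20.9 | ±3.26 | 33% | 94% |
| 0.30 | 60.7 | ±5.56 | 20% | 92% |

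**Which ICC is plausible?** Block loss through drop-out gives a guide. Suppose 5% of fields are missing at random and some participants also lose a share of their fields (34 participants, 200 fields each, all assumed). The ICC is the between-person variance of the missing proportion divided by p(1 − p).
- Two drop-outs each losing one third: their missing proportion is 1/3 + (2/3)(0.05) = 0.367, so p = (32 × 0.05 + 2 × 0.367)/34 = 0.069. Variance = (2/34)(32/34)(0.317²) = 0.0056, ICC ≈ 0.09, DE ≈ 18, factor ≈ 4.3.
- Four drop-outs each losing half: their missing proportion is 0.525, so p = (30 × 0.05 + 4 × 0.525)/34 = 0.106. Variance = (4/34)(30/34)(0.475²) = 0.0234, ICC ≈ 0.25, DE ≈ 50, factor ≈ 7.

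The same sums show the mixing: item missingness is 5% throughout, but the percentage over all fields reads 6.9% or 10.6%.

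**Adherence.** Assume 17 users (1:1 allocation of 34; the ratio is not stated), 30 sessions each (3 per week for 10 weeks, the low end of the general recommendation in the Background), 70% marked and ICC 0.3. A mean of per-participant percentages with a t-interval has half-width ±13.4 points and covers 94%. An interval pooled over 510 sessions would be ±4.0 points and cover 47%. The first is what the adherence wording most naturally describes.

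**The case against.** The strongest objection is that the article never says how these intervals will be computed. It mentions no binomial interval, no pooling and no independence assumption. Interval methods are commonly left to an analysis plan, which is not shown. This stands: a reader might infer that the trial has committed itself to intervals over fields and sessions that are several times too narrow, and the text does not support that. What can be said is conditional. The completeness definition is at field level, and an interval that follows it literally would be too narrow.

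The objection succeeds for adherence. Plans are personal and the professional reviews adherence patient by patient, so one percentage per participant is the natural quantity, and an ordinary interval for its mean is valid.

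The factors also depend on assumed inputs. At ICC 0.01 the loss is only 1.2 to 2 times. This is fair, although an ICC that low requires almost no block loss of data.

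Finally, counting drop-outs' lost fields in overall completeness is not an error in itself. Drop-out has its own outcome and interval, the missing-data pattern will be examined, and participants who stop the intervention are encouraged to complete assessments. That leaves the second completeness figure as a cheap improvement, not a correction.

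**Conclusion.** The point holds for data completeness, in conditional form. An interval computed over fields, as the outcome is worded, would be too narrow by about 1.2 to 2 times at ICC 0.01 and about 1.9 to 9.5 times at ICC 0.05 to 0.30, for 50 to 300 fields per participant. The field count, ICC and percentage missing are assumptions, so no single factor should be quoted as the trial's own.

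For adherence there is no error, only a unit to confirm. It would also go too far to say that the decision on a definitive trial hangs on these intervals. The analysis is descriptive, and the limitations section says that there are no prespecified progression criteria and that the decision will be discussed with stakeholders, drawing also on comparable international studies. Severity is low.

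**What to change.** 1. **Completeness:** calculate the percentage of due fields that are missing for each participant, summarise it across participants, and take the 95% CI from a participant-level t-interval or bootstrap. If the pooled percentage is kept, give it a cluster-robust interval. Say which is used: the intervention group has extra week-10 questionnaires, so the pooled figure weights that group more and the two can differ.
2. **Separate drop-out from item non-response:** report completeness over all due fields and again over fields due before withdrawal.
3. **Adherence:** confirm that the percentage is computed per participant and that its interval is taken across participants.

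The cost is a sentence or two of analysis wording and wider intervals. No new data are needed. Because data collection has finished, the report should say that the unit was clarified at the analysis stage, unless a fuller plan already fixes it.

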### Data Collection From Participants

#### Data From Routinely Conducted Assessments and Clinical Records

Demographic data and height will be recorded at week –3 to –2. Blood tests (cholesterol and glycated hemoglobin), medication, body mass, vital parameters, and incremental cycle ergometry will be recorded 3 times (at week –3 to –2, time point 0, and week 10). Adverse event reporting will take place at week 10.

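### The group comparison of clinical outcomes names no use of pre-randomisation values or stratification factors; baseline adjustment costs almost nothing and would narrow the intervals where the baseline correlation is high

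*Protocol article*

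**What the plan says.** The Analyses section of the protocol article describes the comparison of secondary outcomes in one sentence: "An exploratory group comparison (descriptive analysis and 95% CIs) will be described for the secondary (clinical) outcome measures for both intention-to-treat and per-protocol approaches". Just before it, the section lists what descriptive analysis means: measures of centre and spread for continuous data, counts and percentages for categorical data. It also rules out testing: "Because this is a pilot study, no confirmatory inferential statistical analysis or hypothesis testing will be conducted". No sentence there mentions a baseline value, a covariate or a stratification factor.

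Elsewhere the article provides the material for an adjusted comparison:

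- Randomization section: "Randomization will be stratified by study site, participant sex, and participant exercise capacity". Exercise capacity is peak power per kg in three bands.
- Section on routinely conducted assessments: blood tests, body mass, vital parameters and ergometry are taken at week -3 to -2, time point 0 and week 10 ("incremental cycle ergometry will be recorded 3 times").
- Self-Reported Questionnaires section: kinesiophobia, exercise self-efficacy, depression and anxiety, and quality of life follow the same three time points.
- Study procedures textbox: the order is baseline collection, randomisation, planning session in week -1 (intervention arm only), then time point 0 at discharge.
- Physical Activity and Heart Rate Measurements section: accelerometry takes place only in weeks 8 to 10.

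The Aim section says that clinical outcomes are collected to inform the sample size of a definitive trial.

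**The concern.** The design stratifies on three factors expected to be prognostic and measures most clinical outcomes before allocation. The analysis as described then uses neither. In a trial this small, a well-correlated baseline value is the main available source of extra precision, and it has already been collected.

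Two things are at stake:

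1. **Input for the next trial.** If the definitive trial adjusts for baseline, its planners need the baseline-to-week-10 correlation or the residual SD. The listed summaries supply neither.
2. **Which value is the baseline.** Two measurements precede follow-up, and the Analyses section does not say which would serve as the reference. Time point 0 comes after allocation and after the intervention arm's planning session. Adjusting for it would condition on something the intervention may already have affected.

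**Working it through.** **The plan's own figure.** The article gives no interval width for the clinical outcomes. Its one sample-size figure concerns feasibility: the sample "allows the detection of problems (eg, participant withdrawals) with a prevalence of 7.5% with 95% confidence". It reproduces: 1 - (1 - 0.075)^40 = 0.956. It has no bearing on the clinical comparison.

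**Inputs**

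- N = 34 recruited (Results: "The study was completed with 34 participants recruited by May 2024"); 40 were planned. The number with week-10 data is not given, so 34 is the best case.
- 1:1 allocation: assumed, as the ratio is not stated.
- Correlation r between the week -3 to -2 value and the week-10 value: not given; assumed range 0.3 to 0.9.
- The other covariates are assumed to explain nothing beyond the baseline value.

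**Raw difference**

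Half-width = t(0.975, N - 2) × sqrt(4/N) = 2.037 × 0.343 = 0.70 SD. At N = 40 it is 0.64 SD.

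**ANCOVA with q covariate degrees of freedom**

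Half-width = t(0.975, N - 2 - q) × sqrt[(4/N) × (1 - r²) × (1 + q/(N - 3 - q))]

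The last factor is the average penalty for chance imbalance in the covariates. At N = 34:

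- q = 1: 2.040 × 0.343 × sqrt(1 + 1/30) = 0.711, times sqrt(1 - r²)
- q = 4: 2.048 × 0.343 × sqrt(1 + 4/27) = 0.753, times sqrt(1 - r²)

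| r (assumed) | Baseline only (q = 1) | Raw / adjusted | Baseline, site, sex, peak power (q = 4) | Raw / adjusted |
|---|---|---|---|---|
| 0.3 | 0.68 SD | 1.03 | 0.72 SD | 0.97 |
| 0.5 | 0.62 SD | 1.13 | 0.65 SD | 1.07 |
| 0.7 | 0.51 SD | 1.38 | 0.54 SD | 1.30 |
| 0.8 | 0.43 SD | 1.64 | 0.45 SD | 1.55 |
| 0.9 | 0.31 SD | 2.25 | 0.33 SD | 2.13 |

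For peak power the baseline value is itself one of the covariates, so q = 3. The half-widths are then 0.70, 0.64, 0.53, 0.44 and 0.32 SD.

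**Break-even.** With four covariates, adjustment gains only if sqrt(1 - r²) < 0.699/0.753 = 0.928, that is r above about 0.37. A raw interval twice as wide as the adjusted one needs r of about 0.87 (baseline only) or 0.89 (four covariates).

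**Accelerometry.** With no baseline, only the design factors are available (4 df: site, sex, two for capacity). If they explain 5% to 30% of the variance (assumed), the raw/adjusted ratio is 0.95 to 1.11 under chance imbalance and 1.02 to 1.19 under perfect balance.

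**Use for the next trial.** Under baseline adjustment the required N scales roughly with 1 - r²: 0.75 at r = 0.5, 0.51 at 0.7 and 0.36 at 0.8. This is why the correlation is worth reporting.

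**The case against.** **Silence is not a decision.** The article never calls the comparison unadjusted. An interval for a change or for an adjusted difference would fit its wording, and a covariate list is often left to an analysis plan, which is not shown here. This stands: it cannot be said that the sponsor chose to ignore baseline. What remains is that the section does name its method, defines descriptive analysis as raw summaries, and does not say which of two earlier measurements is the baseline.

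**It is exploratory.** Feasibility and usability are the primary outcomes, no test is planned, and no decision in the article depends on these interval widths. This stands and limits the importance of the point. It is no reason against adjustment, since an adjusted difference with an interval needs no test.

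**Stronger readings that a reader might infer are not supported:**

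- *Intervals twice as wide as necessary.* This needs a correlation near 0.87 to 0.89, and the article gives none. One correlation is also unlikely to fit body mass, blood pressure and questionnaire scores alike.
- *A wrong error estimate.* Leaving out stratification factors tends to make the interval conservative, and the estimate stays unbiased.
- *Results driven by chance baseline differences or unequal arms.* The documents do not show this, and stratification by capacity is meant to limit it for peak power. Block size is not stated, so arm imbalance cannot be worked out from the article.
- *The wrong SD for the next trial.* The article does not say how that trial will be analysed, and a raw SD is a legitimate, cautious planning input.

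**Conclusion.** The point holds as a matter of precision and of information for the next trial, not of validity. As described, the comparison names no use of pre-randomisation values or design factors that exist for most clinical outcomes.

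Over assumed correlations of 0.3 to 0.9, with N = 34 and 1:1 allocation, the raw interval is about 1.0 to 2.3 times as wide as one adjusted for baseline alone, and about 0.97 to 2.1 times as wide as one adjusted for four covariates. The benefit is real for strongly correlated outcomes, and absent or slightly negative for weakly correlated ones. For accelerometry it is small at best. Fewer participants with week-10 data would widen all of these intervals.

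One part depends on no assumed figure: by the article's own sequence, time point 0 is a post-randomisation measurement and is unsuitable as a baseline covariate.

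**What to change.** In the Analyses section, or in the analysis plan if one exists, state the following:

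1. For each continuous secondary outcome with a week -3 to -2 value, report the week-10 group difference with a 95% CI from an ANCOVA on that value, site, sex and baseline peak power as a continuous covariate. This takes 4 covariate df, or 3 for peak power itself. Keep the raw summaries alongside.
2. Report the baseline-to-week-10 correlation and the residual SD for each such outcome.
3. Do not use time point 0 as the baseline covariate, because it follows randomisation and the week -1 planning session.
4. For accelerometry, adjustment for the design factors and the baseline Rapid Assessment of Physical Activity score is optional, with little gain expected.

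The cost is a few sentences, a few lines of code and 3 to 4 degrees of freedom; no new data are needed. The Results section says that collection was complete and analysis under way, so if the model is fixed after group results have been seen, the report should say so. If an analysis plan already specifies an adjusted comparison, a short statement to that effect resolves items 1 and 3, and item 2 only has to be added to the report.
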